### Sample size

Our Toronto work showed an average baseline collision rate of 7.4/10,000 children per year in a sample of 118 elementary schools [28]. Based on this work, traffic calming density had an important association with collision rates with a rate ratio of 1.31 (1.06–1.63) and can be considered an example covariate of interest on which to base our sample size calculations. Traffic calming density had a Poisson distribution and a lambda of 0.44. Therefore, a sample of between 120 and 140 would be required to achieve 95% power at a 0.05 significance level [43]. The existing standard is that there be at least 10 cases for each parameter estimated in a regression model. Our previous model from Toronto had 7 covariates, necessitating at least 70 participant schools. Therefore, by collecting data at up to 125 schools in each of the municipalities, we have sufficient power to detect important rate ratios and the opportunity to compare built environment covariates across geographic locations [42].

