### Sample size

The target sample size is 125 schools per municipality. Walking rates by school varied from 28 to 98% with a mean of 67% in our previous studies [29]. Using walking rates as an outcome and using built environment predictors we have measured before, only 50 schools per municipality are required to achieve 95% power at a .05 significance level [42]. We target a larger sample required for an injury model.

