### Data collection

Collisions involving child pedestrians and bicyclists, ages 4–12, will be extracted from the most recent ten years available of police reported child pedestrian-motorvehicle collisions (MVCs) and bicyclist-MVCs in each municipality. Our partners in each municipality will facilitate the access to these datasets. The file will include the geographical coordinates of the collision, which will be mapped onto school buffers. Collision rates will be estimated using census populations within school buffers. Using 10 years of collision data together generates stable, interpretable child pedestrian collision rates as demonstrated in our published work from Toronto [28].

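### Project 2A's 95% power claim for 120–140 schools conflicts with the confidence interval quoted beside it, which implies about 72% power for RR 1.31 at 125 schools in one city

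*Protocol article*

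**What the plan says.** The Sample size section of Project 2A (Protocol article) starts from earlier Toronto work with an "average baseline collision rate of 7.4/10,000 children per year in a sample of 118 elementary schools". It takes one covariate from that work as its planning example: "traffic calming density had an important association with collision rates with a rate ratio of 1.31 (1.06–1.63"). It adds that "Traffic calming density had a Poisson distribution and a lambda of 0.44" and draws the conclusion "Therefore, a sample of between 120 and 140 would be required to achieve 95% power at a 0.05 significance level". It then carries this over to the programme: "by collecting data at up to 125 schools in each of the municipalities, we have sufficient power to detect important rate ratios", and adds that covariates can be compared across locations.

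The figure also sets the target for Objective 1. The Sample size section there finds 50 schools per municipality enough for walking rates, and then says "We target a larger sample required for an injury model".

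The Data analysis section of Project 2A plans a multivariable Poisson model, with alternatives if there is over-dispersion. Municipality enters as a covariate, and effect modification by municipality is to be evaluated.

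**The concern.** The planning effect and its interval come from 118 schools, almost the number proposed for each city. An interval whose lower limit is 1.06 shows that 118 schools estimated this effect with little room to spare. A study of about the same size, aimed at the same effect, cannot have 95% power unless its schools are much more informative than the Toronto schools, and the protocol gives no reason to expect that.

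The risk lies in how city-level results are read. If 125 schools per city are believed to give 95% power, a null traffic calming result in one city looks like good evidence of no association there. On the quoted precision, an effect of this size would be missed in nearly 3 of 10 cities. Project 3B plans to compile results from Objectives 1 and 2 into municipality-level reports, so the over-reading could reach local decisions.

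**Working it through.** **Inputs (Project 2A, Sample size, unless noted)**
- RR 1.31, interval 1.06–1.63, from 118 schools; ln 1.31 = 0.2700. The level is not stated; 95% is assumed. The limits are symmetric on the log scale: √(1.06 × 1.63) = 1.314.
- Covariate Poisson with λ = 0.44.
- Baseline rate 7.4 per 10,000 children per year. Ten years of data are planned, and the Project 2A Data collection section cites the Toronto work for this: "Using 10 years of collision data together generates stable, interpretable child pedestrian collision rates as demonstrated in our published work from Toronto".
- Significance level 0.05; sidedness is not stated and two-sided is assumed.
- Planned size: up to 125 schools per municipality, so up to 4 × 125 = 500.

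**Step 1. Can 120–140 be reproduced?**
The Signorini formula for Poisson regression with a Poisson covariate is
N·μ = [1.960·√V0 + 1.645·√V1]² / (ln RR)².
- V0 = 1/0.44 = 2.273
- V1 = exp(−0.44 × 0.31 − 0.2700)/0.44 = 1.514
- N·μ = [1.960 × 1.508 + 1.645 × 1.230]² / 0.2700² ≈ 340 baseline collisions

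So N = 140 needs 340/140 = 2.4 expected collisions per school, and N = 120 needs 340/120 = 2.8. At 7.4/10,000 per year over 10 years (0.0074 per child) that is about 330–380 children per school buffer. The section does not give the number of children, so this route neither confirms nor refutes 120–140. The formula as applied here contains no allowance for correlated covariates or over-dispersion.

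**Step 2. What precision does the quoted interval imply?**
- SE at 118 schools = ln(1.63/1.06)/3.92 = 0.1098
- Expected z = 0.2700/0.1098 = 2.46
- 95% two-sided power needs 1.960 + 1.645 = 3.60

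**Step 3. Power at the planned sizes**
SE(n) = 0.1098·√(118/n); power = Φ(0.2700/SE(n) − 1.960).

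| Schools | Power for RR 1.31 |
|---|---|
| 118 | 69% |
| 120 | 70% |
| 125 | 72% (71.6%) |
| 140 | 76% |
| 500 (pooled, common RR) | 99.9% |

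**Step 4. Schools needed and detectable effect**
- 95% power: 118 × (3.605 × 0.1098/0.2700)² = 253.4, so 254
- 80% power: 118 × (2.802 × 0.1098/0.2700)² = 153.1, so 154
- At 125 schools SE = 0.1067, so the detectable RR at 80% power is exp(2.802 × 0.1067) ≈ 1.35

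**Step 5. Size of the discrepancy**
The variance implied by the interval, relative to what 95% power allows, is 253.4/140 = 1.8 to 253.4/120 = 2.1.

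**Step 6. Comparison of two cities, 125 schools each**
SE of the difference in log RR = 0.1067 × √2 = 0.151. Power for a 1.31-fold difference = Φ(0.2700/0.151 − 1.960) ≈ 43%.

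**Step 7. Sensitivity at 125 schools**
- Rounding of the RR and its limits: 69–74%
- One-sided 0.05: 81%
- Interval taken as 90%: 57% two-sided
- Interval taken as 99%: 91% two-sided

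Only a 99% interval together with a one-sided test reaches 95% (95.4%), and nothing in the protocol suggests either.

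**The case against.** The strongest reply is that the main model is not underpowered. The Project 2A analysis is described as a regression with municipality as a covariate, and over up to 500 schools it has over 99% power for a common RR of 1.31. Separate models for each municipality are stated outright only for Objective 1; they reach Project 2A at most through its opening reference back to that objective. This stands, and it limits the point to city-level and between-city results. It does not rescue the text, because 120–140 is set directly beside 125 schools in each municipality and the same sentence promises comparison across locations.

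A second reply is that the 72% is conditional. The interval level, the sidedness, the Toronto model behind the interval and the information per school elsewhere are not given. That is fair for the exact value. The direction is secure under any ordinary reading.

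A third reply is that power computed from an observed effect is circular. Here the protocol itself adopts 1.31 as its planning value; the interval supplies only the standard error.

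Some stronger readings are tempting but unsupported:
- A reader might infer that 120–140 is an arithmetic slip. Step 1 shows that a plausible but unstated exposure per school yields it.
- A reader might infer that 125 falls short of the plan's own requirement. It lies inside the stated range.
- A reader might want a power figure for bicyclist collisions. The document gives no bicyclist collision rate for ages 4–12 near schools, so none can be derived.

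**Conclusion.** The concern holds as an inconsistency between a stated power and the precision quoted beside it. Power for RR 1.31 is about 72% at 125 schools in one city, against the 95% claimed for 120–140. This assumes a 95% interval, a two-sided test and Toronto-like information per school in the other cities.

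The 1.8–2.1-fold gap in variance is consistent with a sample size formula that ignores correlated covariates and over-dispersion, although the planned model is multivariable and over-dispersion is anticipated. The cause itself cannot be established from the document.

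The pooled main effect is unaffected. What is overstated is the reliability of a null finding in a single city and, more so, the ability to detect differences between cities.

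**What to change.** In the Sample size section of Project 2A:
- State per-city power as about 72% for RR 1.31 at 125 schools, with 80% power for an RR of about 1.35.
- Tie the 95% claim to the pooled, municipality-adjusted model in the Data analysis section, assuming a common effect.
- Label city-specific and effect-modification results as lower-powered, to be read from their intervals and not from significance alone.
- State the inputs behind 120–140: expected collisions or children per school, sidedness, interval level, and any allowance for covariate correlation and over-dispersion.

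The cost is wording and a less favourable stated power. No extra schools, data or change of model are needed, and the 125-school target can stay.

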### Anticipated concerns

It is possible that policies used by police attending incidents vary between cities. To address this concern, we will do a sub-analysis of collisions classified as serious or fatal. Research suggests more accurate reporting of serious and fatal injury by police [44–46]. It is also possible that we will not have the collision data from the same time period for each municipality. We will deal with this by basing models on the most recent years when data are available from all municipalities.

#### Project 2B

To analyse the space-time distribution of pedestrian-MVCs and bicyclist-MVCs to understand the complex geography of child and youth injury events and risk factors

### Study design/location/participants/recruitment

Spatial density and space-time clustering analyses will take place to assess the dispersion, concentration and localisation in space and time of all child and youth pedestrian-MVCs or bicyclist-MVCs in the four municipalities in Project 2A.

### Data collection

As in Project 2A, we will use the most recent 10-year period of available police-reported traffic collision data. This project will be conducted municipality-wide, not focussed specifically on school zones as in Project 2A.

### Data analysis

Spatial density analyses (area and road network) will be based on three different outcomes: 1) Counts of collisions per census dissemination area by municipality; 2) Counts of collisions per intersection; 3) Counts of collisions per road segment length. Kernel density (area) and network kernel density (road segment) analysis will be used [47–50]. Local Indicators of Spatial Association and Moran’s I will be used to identify hot spots by dissemination area at the municipal and national level [51]. These results will pinpoint potential hot spots of pedestrian-MVCs or bicyclist-MVCs within and between municipalities across Canada and will examine built environment variables within those hot spots. Space-time clustering analysis will be based on two outcomes: 1) Counts of collisions per dissemination area per month by municipality with child population within the dissemination areas considered as the population at risk; 2) Counts of collisions per school zone, with the population at risk being active transportation counts (from Objective 1). Results will be mapped and analysed statistically.

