### Anticipated concerns

There is the potential that too few crashes will lead to non-significant results in the spatial cluster analysis since the method is pointing at spatial over-representation. This is, however, less likely to be an issue as we are using ten years of historical collision data from 4 cities and we had sufficient power to detect modest associations in our previous work (Toronto) [28].

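### Project 2B's only built environment step looks inside hot spots, which are selected on the outcome, and names no comparison area, so as written it does not serve the project's risk-factor aim

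*Protocol article*

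**What the plan says.** All references are to the protocol article.

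- **Aim (Project 2B heading).** The space-time distribution of collisions is analysed "to understand the complex geography of child and youth injury events and risk factors". The list of research program objectives also names risk factors for this project.
- **Coverage (Project 2B, Data collection).** "This project will be conducted municipality-wide, not focussed specifically on school zones as in Project 2A".
- **How hot spots are found (Project 2B, Data analysis).** Local Indicators of Spatial Association and Moran's I "will be used to identify hot spots by dissemination area at the municipal and national level". The inputs are collision counts.
- **Built environment step (same section).** The results "will examine built environment variables within those hot spots". No other sentence in Project 2B mentions built environment variables.
- **Space-time clustering (same section).** One analysis uses monthly counts per dissemination area, "with child population within the dissemination areas considered as the population at risk". The other uses counts per school zone, with active transportation counts as the population at risk. Neither names a built environment covariate.
- **Closing statement (same section).** "Results will be mapped and analysed statistically".

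**The concern.** A risk factor is established by a contrast: the feature must be more common where the outcome is frequent than where it is not, or the outcome must be more frequent where the feature is present. Project 2B first selects areas because they have many collisions and then examines the built environment inside them. That is the areal equivalent of a case series without controls. It gives the prevalence of a feature among high-collision areas and leaves out the prevalence elsewhere, which is needed to interpret it. Better hot-spot detection does not help, because even perfectly located hot spots would lack a comparator.

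At stake is how the result is read. Features common throughout a city, such as arterial roads, traffic lights or transit stops, could appear as hot-spot characteristics whether or not they are associated with collisions. Project 3B (Study design) compiles information from Objectives 1 and 2 into local data reports for use with the municipal toolkit, so a descriptive finding could reach people who decide on road design.

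**Working it through.** Project 2B states no sample size, power or error rate, so there is no figure to reproduce. Its Anticipated concerns section says only that "we had sufficient power to detect modest associations in our previous work (Toronto"). The check is therefore a reading of the text, followed by a short illustration.

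**Step 1: set the aim against the analysis.**

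| Element of Project 2B | What the text gives | Contrast with other areas? |
|---|---|---|
| Aim | Geography of events, and risk factors | Needed for the risk-factor part |
| Density analyses | Counts per dissemination area, intersection and segment length; kernel density | None involving the built environment |
| Hot-spot detection | Local clustering by dissemination area | Outcome only |
| Built environment step | Examined within hot spots | None named |
| Space-time clustering | Counts and a population at risk | No built environment covariate |

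No row supplies the contrast that the risk-factor part of the aim requires.

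**Step 2: see whether another project supplies it.**

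- Project 2A regresses collisions on built environment predictors, but for ages 4–12 in buffers around the sampled schools.
- Project 2C is municipality-wide, but compares rates before and after installation of features with known dates.
- Project 2D compares injury sites with control sites, but for injured bicyclists seen at three emergency departments.

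Each has a valid contrast for its own question. None compares the built environment of hot spots with that of the rest of the municipality.

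**Step 3: illustrate the consequence.** The prevalences are assumed and do not come from the article. Let p_hot be the proportion of hot-spot areas with a feature and p_other the proportion of other areas with it.

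- Prevalence ratio = p_hot / p_other
- Odds ratio = [p_hot / (1 − p_hot)] / [p_other / (1 − p_other)]

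With p_hot = 0.60, the hot-spot odds are 0.60 / 0.40 = 1.5.

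| p_other | Odds elsewhere | Prevalence ratio | Odds ratio | Reading |
|---|---|---|---|---|
| 0.20 | 0.20 / 0.80 = 0.25 | 0.60 / 0.20 = 3.0 | 1.5 / 0.25 = 6.0 | More common in hot spots |
| 0.60 | 0.60 / 0.40 = 1.5 | 0.60 / 0.60 = 1.0 | 1.5 / 1.5 = 1.0 | No difference |
| 0.80 | 0.80 / 0.20 = 4.0 | 0.60 / 0.80 = 0.75 | 1.5 / 4.0 = 0.375 | Less common in hot spots |

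A hot-spot-only analysis reports 60% in all three rows. The choice of 60% is not critical: for any p_hot strictly between 0 and 1, the odds ratio can be above, at or below 1 depending on p_other, which the described step does not measure.

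**The case against.** The strongest reply is that Project 2B is mainly descriptive. Its design section speaks of dispersion, concentration and localisation, whereas 2A and 2D are set up to estimate associations and 2C to estimate an effect. Describing features in located clusters is a legitimate way to generate hypotheses. This stands in part: it confines the point to 2B's risk-factor aim and leaves detection and mapping untouched. It does not remove the point, because the aim itself names risk factors.

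A second reply is that a condensed article may leave the contrast to a fuller document. Here, however, the article states where built environment variables are examined, and that location does not match the aim. The point rests on what is stated.

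Four stronger readings are tempting, and the article does not support them:

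- **That the rest of the city is deliberately excluded.** The article does not say this. It names no other location, and its closing statement on statistical analysis is too general to confirm or rule out a comparison.
- **That 2B can yield no information at all on risk factors.** Differences in collision intensity among hot spots, within and between municipalities, could give some information over a restricted range.
- **That Objective 2 as a whole lacks contrasts.** Projects 2A, 2C and 2D have them.
- **That uncompared feature lists will be issued to municipalities as risk factors.** The article says only that information from Objectives 1 and 2 feeds the local reports. Misreading is a possibility, not a stated plan.

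**Conclusion.** The point holds in a limited form. The one built environment step described for Project 2B concerns areas chosen on the outcome and has no stated comparator, so it can describe hot spots but cannot show whether a feature is over-represented in them. This is a mismatch between one stated aim and its stated analysis, and it should be corrected. It does not threaten the rest of Objective 2.

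Its numerical size cannot be derived from the article. The odds ratios from 0.375 to 6.0 rest on assumed prevalences and show only that one hot-spot figure fits associations in either direction or none. The conclusion also assumes that the step is carried out as worded, with no contrast added from a document not shown.

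**What to change.** In Project 2B, Data analysis, replace the phrase on examining variables within hot spots with one of two statements:

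1. Built environment variables from the spatial database will be compared between hot-spot and non-hot-spot dissemination areas in the same municipality; or
2. Collision counts in all dissemination areas will be modelled on these variables.

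Either version should take child population as the population at risk, adjust for area deprivation and allow for spatial dependence. The second avoids splitting a count outcome in two. The unit should be the dissemination area, because that is the only unit for which the article gives a hot-spot method.

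If neither is wanted, keep the step, label it as descriptive and say in the aim and in the local reports that it is not evidence on risk factors.

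The cost is small. Collision data already cover the whole municipality, and the municipality-wide Project 2C also draws predictors from the spatial database. The downside is additional GIS extraction and analysis outside school buffers. The comparison would be limited to variables held in the spatial database, because those from the school site surveys do not exist for other areas.

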### Study design

A cross-sectional design will be used that will include primary data collection of active transportation around schools and data from secondary sources related to the built environment, social and individual factors.

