### Location and participants

A sample of 125 elementary schools (depending on the number of eligible schools in the jurisdiction) will be chosen in four urban regions (Montreal, Toronto, Calgary, Vancouver). Regular program elementary schools (typically Kindergarten-Grade 8) will be included. Schools with older grades will be excluded as older students have very different school transportation patterns, in part due to developmental skills and larger attendance boundaries for middle and high schools. Schools focused on special programs such as arts-based curricula, French immersion, and special needs will be excluded as their students travel further and may be more likely to be driven. Eligible schools will be stratified by Walk Score® (related to population density and urban form) and socioeconomic status (SES; After Tax-Low Income Cutoff [AT-LICO]) in order to represent several urban and suburban built environment types and to enable some exploration of active transportation and SES [31, 33]. Local knowledge users may participate in selecting municipalities and schools. Across each selected SES/built environment stratum, the list of schools will be randomly ordered, and schools will be observed in the order of randomization until the maximum sample in each municipality is met.

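### Project 2B's school-zone clustering sets ten years of child and youth collisions against a cross-sectional count of active arrivals at elementary schools, so zones with few active arrivals can be flagged without higher risk per school trip

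*Protocol article*

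**What the plan says.** **Collisions.** Under Project 2B, Study design/location/participants/recruitment, the analysis concerns the "localisation in space and time of all child and youth pedestrian-MVCs or bicyclist-MVCs in the four municipalities in Project 2A". Under its Data collection heading, "we will use the most recent 10-year period of available police-reported traffic collision data". No heading of Project 2B limits the school-zone outcome by age, hour, weekday or season.

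**Population at risk.** Project 2B, Data analysis, lists two space-time outcomes. The first is "Counts of collisions per dissemination area per month by municipality with child population within the dissemination areas considered as the population at risk". The second is "Counts of collisions per school zone, with the population at risk being active transportation counts (from Objective 1").

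**Where the count comes from.** Objective 1, Study design: "A cross-sectional design will be used that will include primary data collection of active transportation around schools". Objective 1, Location and participants: "Regular program elementary schools (typically Kindergarten-Grade 8) will be included", and "Schools with older grades will be excluded as older students have very different school transportation patterns". Under Data collection the observers record travel mode to school, and under Data analysis the active modes are walking, bicycling and other active transportation.

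**Contrast.** Project 2A restricts collisions to ages 4–12, estimates rates on census populations within school buffers, and enters the active transportation proportion as a predictor.

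**The concern.** A cluster analysis compares observed counts with counts expected in proportion to the population at risk. That works only if the events come from that population. Here the two differ in three respects: age (all children and youth against pupils of elementary schools), trip (any collision in the zone against arrivals at school) and calendar time (ten years against a cross-sectional observation). The article's own reason for leaving out schools with older grades, that older students travel differently, means the count cannot stand in for them.

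Any part of the collision count that does not rise and fall with active arrivals inflates the apparent rate where arrivals are few and deflates it where they are many. The error therefore has a direction: low-walking schools tend to look dangerous. Project 3B says that information from Objectives 1 and 2 will be compiled into municipality and school/neighbourhood reports, so a false hot spot could reach the people who decide on changes.

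**Working it through.** The article gives no power, event or rate figure for this outcome, so there is nothing to reproduce. The check asks how large an artefact the mismatch could produce.

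**Inputs from the article**
- School walking rates of 28% to 98%, mean 67% (Objective 1, Sample size).
- Baseline collision rate of 7.4 per 10,000 children per year (Project 2A, Sample size).

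**Assumptions, not in the article**
- Equal risk per counted school trip in every zone.
- Equal arrival totals at every school, so the active count is proportional to the walking rate W.
- In a zone at the 67% mean, a share s of collisions scales with the active count. The rest, 1 − s (older youth, non-school trips), does not depend on it.

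**Apparent relative rate per active arrival**, against a zone at the mean:

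RR(W) = [s × (W/67) + (1 − s)] / (W/67) = s + (1 − s) × 67/W

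with 67/28 = 2.393 and 67/98 = 0.684.

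| Share unrelated (1 − s) | RR at 28% | RR at 98% | Spread |
|---|---|---|---|
| 0 | 1.00 | 1.00 | 1.0-fold |
| 0.25 | 0.75 + 0.25 × 2.393 = 1.35 | 0.75 + 0.25 × 0.684 = 0.92 | 1.5-fold |
| 0.50 | 0.50 + 0.50 × 2.393 = 1.70 | 0.50 + 0.50 × 0.684 = 0.84 | 2.0-fold |
| 0.75 | 0.25 + 0.75 × 2.393 = 2.04 | 0.25 + 0.75 × 0.684 = 0.76 | 2.7-fold |

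The true relative rate per school trip is 1.00 in every cell. The first row shows that the artefact disappears if every collision comes from counted trips.

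**Would it be noticed as a cluster?** The clustering statistic is not named, so a one-zone Poisson test at a nominal one-sided 5% serves as a rough guide. Assume 1,000 children per zone: 7.4/10,000 × 1,000 × 10 = 7.4 collisions in ten years.
- If 7.4 is the expected count for the zone in question, a flag needs 13 or more. The chance is 3.9% at RR 1.0 and 49% at RR 1.70. For 500 to 2,000 children (expected 3.7 to 14.8), the chance at RR 1.70 runs from 30% to 76%.
- If 7.4 belongs to the average zone, the expected count at a 28% school is 7.4 × 28/67 = 3.1 and a flag needs 7 or more. The chance is then 3.8% at RR 1.0 and 28% at RR 1.70.

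On either footing, the false-flag rate rises well above nominal.

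**Calendar time.** If walking changed by the same factor in all zones, observed-to-expected comparisons between zones are unaffected. If it changed differently, a count from one period assigns the wrong expected number to the other years, and the zones that changed most can appear as clusters.

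**The case against.** **The numerator may be narrower than it looks.** The school-zone outcome itself says only collisions per school zone; the reference to all children and youth is Project 2B's general scope. Its Data collection paragraph opens by referring back to Project 2A, which uses ages 4–12, and a condensed article may leave a filter to the full protocol. This stands in part. It is the weaker reading, because that sentence concerns the ten-year police data. Even if it brought in ages 4–12, the trip and calendar-time mismatches would remain. What is objectionable is the stated choice of population at risk, not an omitted detail.

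**Older youth are not wholly missing.** A reader might infer that no one aged 13–17 is in the count. The article does not support that: K–8 schools reach about age 13–14, and the 13–17 band is Project 2D's definition. Project 2B states no upper age.

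**The size is assumed.** A reader might take the 13–17 share of ages 4–17, 5/14 = 36% under equal risk per year of age, as the bias. It is not: a share that is uniform relative to the count cancels when observed is compared with expected. Only variation between zones matters, and the article gives no figure for it. This stands.

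**The consequence can be overdrawn.** A reader might infer that the clusters will be reported as excess risk to elementary pupils, or that any change in walking will produce a cluster. The article says neither. Project 2B's aim is the geography of child and youth injury, Project 2A addresses risk near schools with a better-matched structure, and the dissemination-area outcome already uses child population.

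**The count may not be a single visit.** The number of observation days is not given. But the design is cross-sectional and nothing points to counts spread over the ten years.

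**Conclusion.** The concern holds for Project 2B's second space-time outcome only. As written, its collisions and its population at risk differ in trip type and calendar time and, on the more natural reading, in age. Following the plan would inflate apparent risk where active arrivals are few.

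The size is illustrative: a 1.5-, 2.0- or 2.7-fold spread between schools at 28% and 98% walking, if one quarter, half or three quarters of collisions in an average zone are unrelated to counted arrivals and arrival totals are equal. The direction follows from the structure; the amount depends on shares that the article does not give. The temporal part rests on walking having changed differently between zones. The dissemination-area outcome is unaffected.

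**What to change.** Choose one of two routes for the school-zone outcome and state it.

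1. **Match the collisions to the count.** Limit collisions to the ages of the grades in the observed schools. Ages 4–12 would be close but not exact, because a K–8 count includes some pupils aged 13 or older. Restrict to school-day travel times as the main or a sensitivity analysis, and treat the outcome as spatial only. Since Objective 1 observes travel to school, trips home would still be represented by proxy, and pupils of other schools in the buffer would remain among the collisions; say so.
2. **Match the population to the collisions.** Use the census child population in the school buffer as the population at risk and enter the active transportation measure as a covariate, as in Project 2A.

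Both use data already planned. Route 1 costs events: at 7.4 per 10,000 per year, an assumed 1,000 children give about 7 collisions in ten years before any hour restriction, which sharpens the sparse-data concern the article itself raises. That is why the hour restriction may fit better as a sensitivity analysis. Route 2 keeps the events but yields rates per resident child, not per active traveller. The dissemination-area analysis needs no change.
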